**Figure 4 BMJOPEN2015010313F4:**
[figure not shown]
Follow-up form.

**Figure 5 BMJOPEN2015010313F5:**
[figure not shown]
Withdrawal form.

An additional reason for carrying out the study is to determine whether participants can tolerate taking medication in the evening. This is prospectively measured. Participants self-report AEs associated with dosing time and whether nocturnal diuretic dosing has been acceptable to them and whether falls and fractures are increased as a potential surrogate for nocturnal hypotensive events.

### Statistics

The primary outcome will be a comparison of time to first event comparing morning versus evening dosing allocation. This outcome will be analysed using a Cox proportional hazards model including treatment group as a covariate. The p value for the treatment effect will be based on the Wald statistic. Point estimates and 95% CIs will be calculated for the treatment effect HR. Time to event curves will be based on cumulative incidence functions. Time to event secondary outcomes will be analysed using similar methods. The proportionality of hazards assumptions will be assessed using Cox models including treatment group by log (time) interactions.

Serious AEs and AEs will be tabulated by treatment group by system organ class and preferred term. All main analyses will be on an intention-to-treat basis.

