## Randomisation

### Computer randomisation

Randomisation is carried out centrally using randomly generated bits (0 and 1 s) which are then allocated to participants (0=morning, 1=evening) sequentially. Randomised status is confirmed by automated email sent to the participant.

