### Sample size: evidence of feasibility and power calculation

For a two-sided test to detect a HR of 0.8 for the primary outcome (evening dosing vs morning dosing) at 80% power, 631 events are needed. Based on the anticipated profile of participants, a trial with an average 4-year follow-up period would need to randomise 9780 participants. Since the primary analysis is intention to treat and because few participants are likely to withdraw consent for record-linkage follow-up, only relatively minor (<5%) inflation of the 9780 participants is required to compensate. A target of 10 269 participants will be randomised. Note that falling cardiovascular event rates in the UK may require a revision of the sample size.

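### The primary Cox model names treatment group as its only covariate: valid and consistent with 631 events, but it forgoes about 1 to 6 points of power that baseline adjustment could bring

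*Protocol article*

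**What the plan says.** The Statistics section of the protocol article fixes the primary model, test and summary. On the model it says: "This outcome will be analysed using a Cox proportional hazards model including treatment group as a covariate". The test is a Wald test, and the summary is the estimated HR with its 95% CI. It names no baseline covariate or stratum. Secondary time-to-event outcomes follow similar methods.

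The section on computer randomisation states: "Randomisation is carried out centrally using randomly generated bits". The bits are assigned to participants in sequence, and no stratification or minimisation is described. Box 1 admits adults from 18 years with any form of treated hypertension. Box 2 sets no limit on vascular history in either direction.

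The sample size section assumes an HR of 0.8 with a two-sided test and concludes: "at 80% power, 631 events are needed". From this it derives 9780 participants with 4 years of follow-up on average, inflated to a target of 10 269. It does not say whether the HR of 0.8 is unadjusted or conditional on baseline covariates.

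**The concern.** With eligibility this broad, vascular risk at entry probably varies widely. Neither the allocation method nor the model as written uses that variation. In a Cox model, leaving out strong predictors attenuates the treatment HR toward 1. Unlike in linear regression, adding them does not shrink the standard error of the treatment effect; the gain comes from removing the attenuation.

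The margin is thin. The trial is sized at 80% power, and the inflation of under 5% covers only withdrawal of consent for record linkage. The sample size section warns that falling event rates may require a revision, and the Withdrawal section expects some participants to leave their allocated dosing time, which dilutes an intention-to-treat contrast. A few points of power are worth having if they need no extra participants.

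**Working it through.** **1. Reproduce the stated figure.** Inputs from the article: HR 0.8, two-sided test, 80% power. Assumptions: alpha 0.05 (not stated, inferred from the 95% CI) and 1:1 expected allocation.

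Schoenfeld: D = 4(z₀.₉₇₅ + z₀.₈₀)² / (ln 0.8)² = 4(1.960 + 0.842)² / (0.2231)² ≈ 631. This matches exactly. Freedman's formula gives 636, and a one-sided test would give 497. The stated number is therefore a standard calculation without covariates, consistent with the stated model. Like that calculation, what follows ignores the interim looks.

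**2. Set up the comparison.** Hazard for a participant with score Z ~ N(0,1): λ · exp(sZ) · HR^(evening), followed for 4 years. λ is chosen so that cumulative incidence is 631/9780 = 6.45%. The score SD, s, is an assumption, varied from 0.5 to 1.2. The C-index is the value implied by s under proportional hazards.

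The HR that a treatment-only Cox model estimates is the solution β of its limiting score equation, ∫[f₁ − p(f₀ + f₁)]dt = 0, with p = S₁e^β / (S₀ + S₁e^β). Here S and f are the survival and density in each arm, averaged over Z.

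Power = Φ(√(631/4) · |ln HR| − 1.96), with √(631/4) = 12.56. Check at HR 0.8: 12.56 × 0.2231 − 1.96 = 0.84, giving 80.0%.

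**3. Results** (point differences are from unrounded values)

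| Score SD | C-index | If 0.8 is conditional: treatment-only HR | Treatment-only power | Points below adjusted 80.0% | If 0.8 is unadjusted: conditional HR | Adjusted power |
|---|---|---|---|---|---|---|
| 0.5 | 0.63 | 0.8016 | 79.3% | 0.7 | 0.7984 | 80.7% |
| 0.7 | 0.67 | 0.8035 | 78.5% | 1.6 | 0.7964 | 81.6% |
| 0.8 | 0.69 | 0.8048 | 77.8% | 2.2 | 0.7951 | 82.1% |
| 1.0 | 0.73 | 0.8084 | 76.1% | 3.9 | 0.7912 | 83.7% |
| 1.2 | 0.75 | 0.8133 | 73.7% | 6.3 | 0.7858 | 85.7% |

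Worked line, SD 1.0: ln 0.8084 = −0.2127; 12.56 × 0.2127 − 1.96 = 0.71; Φ(0.71) ≈ 76%.

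**4. In events.** Information on the log HR scales with its square, so the effective loss is 1 − (ln HR_treatment-only / ln 0.8)². At SD 0.5: 1 − (0.2211/0.2231)² ≈ 2%, about 11 of 631 events. At SD 1.2: 1 − (0.2067/0.2231)² ≈ 14%, about 90 events.

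**5. Simulation check.** 3000 trials of 9780 participants per setting, conditional HR 0.8, Wald tests:

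| Score SD | Unadjusted power | Adjusted power | Difference, points (SE) |
|---|---|---|---|
| 0.5 | 80.6% | 81.4% | 0.8 (0.3) |
| 0.75 | 78.9% | 80.3% | 1.4 (0.4) |
| 1.0 | 75.5% | 79.9% | 4.4 (0.5) |

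The standard error of the log HR was 0.080 in both models throughout. At SD 1.0 the mean log HR was −0.212 unadjusted and −0.224 adjusted. The gain is therefore the removal of attenuation.

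**The case against.** The strongest reply is that nothing here is an error. Under simple randomisation a treatment-only Cox model with a Wald test is valid, and the sample size matches it. That stands in full: this is a choice between two legitimate analyses, one of them more efficient.

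A reader might infer that the trial falls short of its stated 80%. The article does not support that. If 0.8 is the HR that the stated model estimates, power is 80% and adjustment is a bonus. The shortfall appears only if 0.8 is the conditional HR, and the article does not say which it is. The direction is the same either way.

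A reader might also take a loss of several points as established. It is not, because the article reports neither a baseline risk distribution nor the strength of any predictor. At a C-index of 0.63 the difference is under 1 point. The calculation also adjusts for the whole simulated score. Age, sex and prior MI or stroke would recover only the part of the risk that they capture.

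The text says the model includes treatment group; it does not exclude other covariates, and a fuller protocol or analysis plan may add some. Treatment-only is still the natural reading, since the sentence fixes model, test and summary together. If a fuller document differs, the two should be reconciled.

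Chance imbalance adds little to the case: with about 10 000 participants it is expected to be small, and the unadjusted test already allows for it. Nor is adjustment shown to be free. Linkage is described for detecting outcomes, and no look-back before randomisation is described.

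**Conclusion.** The point holds as an efficiency recommendation. The primary model as written is valid and agrees with 631 events and 80% power, but it forgoes a gain of about 1 to 6 points. That range rests on an assumed risk-score SD of 0.5 to 1.2, two-sided alpha 0.05, 6.45% cumulative incidence over 4 years, and adjustment that captures the whole score. The gain from the covariates proposed below would be smaller to the extent that they miss part of that risk. The article supports no finding that the stated power is wrong or that the planned test is biased in its type I error.

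**What to change.** In the Statistics section, before any unblinded interim look:

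- Define the primary analysis as a Cox model with treatment group, age (continuous) and sex. Add prior MI or stroke if it is available from baseline data or from linkage before randomisation.
- Use the same model at the interim analyses after about 50% and 75% of the target outcomes.
- Report the treatment-only HR with its 95% CI as a sensitivity analysis.
- In the sample size section, state whether the 0.8 is the unadjusted or the conditional HR.

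The cost is a few sentences of text. The primary HR becomes conditional on the covariates, so it answers a slightly different question from the unadjusted HR reported beside it. Prior-event status may need a linkage look-back. The 631 events can stay as they are.

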### Data collection and retention

This study will capture data directly from patients or their nominated surrogates and by record linkage to hospitalisations and deaths. Consent will be gathered from patients to have access to their healthcare records, diagnostic or death data, their acute care summary, their paper or electronic records, their paper or electronic primary care records, and, permission to contact their physicians for further data. Data will be validated at point of entry into the TIME database and at regular intervals during the study. Data will be held securely within the Medicines Monitoring Unit (MEMO) at Ninewells Hospital and Medical School. To enable evaluations and/or audits, the investigators will keep records, including the identity of all participating patients, all original informed consent data, AE data and any source documents. The records will be securely retained and archived by the study sponsor according to ICH, GCP and local regulations. Participating individuals will be able to have sight of their own data on request and will be allowed to comment on perceived inaccuracies therein.

### Data protection

The study will comply with the requirements of the Data Protection Act 1998 with regard to the collection, storage, processing and disclosure of personal information and will uphold the Act's core principles. Access to collated participant data will be restricted to appropriate study staff. Published results will not contain any personal data that could allow identification of individual participants.

### Sample size: evidence of feasibility and power calculation

For a two-sided test to detect a HR of 0.8 for the primary outcome (evening dosing vs morning dosing) at 80% power, 631 events are needed. Based on the anticipated profile of participants, a trial with an average 4-year follow-up period would need to randomise 9780 participants. Since the primary analysis is intention to treat and because few participants are likely to withdraw consent for record-linkage follow-up, only relatively minor (<5%) inflation of the 9780 participants is required to compensate. A target of 10 269 participants will be randomised. Note that falling cardiovascular event rates in the UK may require a revision of the sample size.

## Substudies

### Home BP substudy

Randomised members of the TIME study are asked, during enrolment, if they are prepared to participate in a substudy and submit home BP readings. Participants who own their own home BP monitor are asked to record and submit BP readings at baseline and then regularly throughout the study. All types and brands of home BP monitors are accepted. A comparison of data collected from non-validated versus validated equipment will be conducted. Participants are issued with instructions to take and submit three sets of readings, morning and evening, for 4–7 days. Specific advice is provided about how to take the measurements in accordance with National Institute for Health and Care Excellence guidelines. The results will demonstrate the effect on home BP of morning versus evening dosing and may help validate adherence to nocturnal dosing.

### Cognitive function substudy

Hypertension has been shown to be a predictor of mild cognitive decline.^28^
^29^ Previous studies have indicated that, particularly at age ≥70 years,^30^
^31^ BP-lowering has relatively little impact on the rate of cognitive decline; but most trials used morning dosing only. The main purpose of cognitive testing in TIME will be to detect temporal change, particularly any sustained reduction in performance, associated with time of antihypertensive dosing. We propose to use combined telephone testing with the Montreal Cognitive Assessment Test and the Trends in Cognitive Sciences^29^ to assess cognitive function in consenting participants in the TIME trial. Previous experience shows that testing takes between 15 and 30 min and is well tolerated by patients.

### Genetics substudy

All participants will be asked if they are prepared to consent to participate in a genetics substudy where their DNA will be bio-banked for possible future genetic studies. Participants who consent will be asked to provide a cheek swab or saliva collection by post.

## Competing studies

We are not aware of any competing studies that would conflict with the TIME study.

### Early stopping

The Independent Data and Safety Monitoring Committee (IDMC) will review un-blinded study results on a regular basis. Taking a balanced view of all accumulated data, levels of statistical significance and the seriousness of events the IDMC might recommend stopping of the study because of an excess of serious AEs in the evening dosing group. The IDMC will also have the opportunity to make a recommendation of early stopping because of overwhelming evidence of benefit from evening dosing based on interim analyses after approximately 50% and 75% of the target number of adjudicated study outcomes have been observed. Overwhelming evidence of benefit is defined as evidence of benefit of evening dosing versus morning dosing (p<0.001).

## Ethics and dissemination

### Steering committee and IDMC

The TIME steering committee oversees the appropriate scientific and ethical conduct of the trial, provides advice to the Study Sponsor, advises on the conduct and analysis of the study, and approves all publications and substudies. The Committee will operate through meetings, teleconferences and emailings. The Steering Committee will be made up of invited experts, the Chief Investigator, the chair of the end-point Committee plus the coapplicants. The Steering Committee will meet at least annually.

The IDMC is completely independent and comprises experts in the field including clinicians with experience in hypertension and an expert trial statistician. The committee receives un-blinded data and has the power to recommend modifications to the conduct of the study, including early discontinuation based on a risk/benefit assessment of the study data. It will meet at least annually and report to the Steering Committee.

### Sponsorship: monitoring, audit, quality control and quality assurance

The study sponsor is the University of Dundee, who are responsible for monitoring and quality assurance. MEMO has conducted independent penetration testing of the TIME website and the Tayside Medical Science Centre (TASC) is assisting MEMO in ensuring quality control for the study. The pilot study was funded by the British Hypertension Society; the full trial is funded by the British Heart Foundation.

### Protocol amendments

Changes in research activity, except those necessary to remove an apparent, immediate hazard, will be reviewed and approved by the Chief Investigator and Sponsor. Amendments to the protocol will be submitted in writing for approval by the appropriate regulatory and ethical authorities prior to implementation.

### Collaborating investigators

Collaborating investigators will be responsible for dealing with the local issues of bringing the trial to the attention of possible participants either in clinics or in primary care. Since all patients by their own volition decide to go to the study website and sign up, the usual investigator/study subject relationship is not present.

### Confidentiality

All data will be held securely with restricted access. Clinical information will not be released without the written permission of the participant, except as necessary for auditing by the sponsor, its designee, regulatory authorities or the research ethics committee.

### Trial registration

TIME is registered as ISRCTN: 18157641 and with a UKCRN ID: 17071. The trial is performed in line with Good Clinical Practice guidelines and International Society of Pharmacoepidemiology (ISPE) Good Pharmacoepidemiology Practice Guidance.^28^

### Dissemination

The results of the trial will be published in a peer-reviewed scientific journal and made available to participants.

## Discussion

The trial design of TIME allows a large study to be undertaken efficiently and cost-effectively by maximising the benefits of modern technology, including use of an electronic case report form and following up patients using record linkage. All data are entered directly by participants, thereby helping to reduce researcher time and costs. Participant's GPs are made aware of their participation in the study but there is no significant workload implication and GPs are not required to submit data. The study allows participants to self-enrol, consent and provide data in a secure online environment. The TIME study has been awarded a grant from the BHF to write to 300 000 patients across the UK to achieve its target of randomising over 10 000 participants.

If the TIME study shows definite benefits of dosing antihypertensive medication in the evening rather than the morning, this would represent the most cost-effective advance in the treatment of hypertension and the prevention of CV disease in recent years. TIME will also establish whether participants can tolerate nocturnal dosing and whether there are any AEs of nocturnal versus morning dosing.
